#### Power calculation

The sample calculation was run via an a priori sample size calculator for Student’s *t* test. Cohen’s d was calculated on the basis of the results of (1) Mo’tamedi et al. [14], concerning the Migraine Disability Assessment scale score under acceptance and commitment therapy and under the control condition (this is the only study conducted in chronic migraine patients in which the Migraine Disability Assessment scale [38], which is one of our primary outcome measures, was used, although it tests the efficacy of a stress-oriented psychotherapeutic intervention which is different from WBT) and (2) Fava et al. [26], which tests the efficacy of WBT in a sample of patients with generalized anxiety disorder using, as the outcome measure, the Psychological Well-being scale [49], which is one of our secondary outcome measures. A Cohen’s d of 2.76 was obtained from Mo’tamedi et al. [14] and a Cohen’s d of 1.38 was obtained from Fava et al. [26]. Setting the power at 0.95 and the two-sided alpha at 0.05, a minimum sample size of 5 per group (two-tailed hypothesis) was obtained on the basis of Mo’tamedi et al. [14] and a minimum sample size of 15 per group (two-tailed hypothesis) was obtained on the basis of Fava et al. [26]. Thus, we will enroll 15 subjects per group for a total of 30 subjects. In case of drop-out, new enrolment will be run in order to have a final sample size of 15 subjects per group who complete the trial.

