**Methods:**

The current intervention will use a randomized controlled trial design, wherein 30 outpatients with chronic migraine will be randomized (1:1) to well-being therapy (*n* = 15) or to a control condition (*n* = 15). Primary outcomes include the level of disability caused by migraine and the frequency, duration, and intensity of migraine attacks; the secondary outcomes focus on anxiety, depression, psychological well-being, euthymia, and distress. Primary and secondary outcomes will be assessed at baseline, after sessions 4 and 8, and at 3-month follow-up. The Ethical Review Boards at the University-Hospital Careggi has approved the study (5th December 2017).

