### Randomization

Following eligibility determination, participants will be randomly assigned to either WBT or a control condition. Block randomization of size two will be used. The two groups will be balanced for age, sex, education, and headache severity. The allocation schedule has been created by the principal investigator (FC) using a computerized random number generator and is concealed to the investigators responsible for enrollment. When a registered patient is randomized, the investigator will contact the principal investigator who will communicate the assigned treatment group. Single blindness will be ensured.

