### Feasibility, acceptability, and participant satisfaction

Measures of feasibility include the ability to recruit the intended population from the SOD Headache Centre and Pharmacologic Clinic of the University Hospital Careggi of Florence, participant willingness to be randomized, and session attendance. In addition, the widely used Client Satisfaction Questionnaire-8 [40] is proposed. The credibility of treatment rationale and expectancy for improvement are evaluated via the Credibility Expectancy Questionnaire [41], which has been shown to be predictive of clinical outcomes in previous treatment trials and was adapted to include questions on expectancies regarding the likelihood of reduction of headache symptoms.

To maintain the blindness of the IEs, these acceptability and satisfaction measures will be administered at the end of the treatment period (session 8) by RAs not otherwise involved in the study.

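### The replacement rule defines the final sample as 15 completers per arm, a target that blocks of two cannot in general deliver and that conditions the comparison on completion

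*Protocol article*

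**What the plan says.** The Power calculation section sets 15 patients per group, 30 in total, and adds that if patients drop out "new enrolment will be run in order to have a final sample size of 15 subjects per group who complete the trial". It gives no expected drop-out rate and no inflation of the sample size.

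The abstract (Methods) says that "30 outpatients with chronic migraine will be randomized (1:1") to two arms of 15. The Randomization section says "Block randomization of size two will be used", with an allocation schedule concealed from those who enrol. It does not say how a replacement patient is allocated.

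The section on feasibility, acceptability and satisfaction names the ability to recruit, "participant willingness to be randomized, and session attendance" as feasibility measures, plus satisfaction and credibility questionnaires. The Data analysis plan repeats recruitment, willingness, attendance and satisfaction. Neither section lists a drop-out or retention rate. The Data analysis plan says that the analysis is mainly descriptive and that ANCOVA will compare means. It names no analysis set.

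**The concern.** Randomisation makes the arms comparable at entry. A sample defined by who finishes is comparable only if finishing is unrelated to outcome, or related to it in the same way in both arms. One arm receives a psychotherapy and the other receives lifestyle information, so drop-out could differ in amount and in kind. If patients who are doing badly leave one arm more often and are replaced by patients who stay, that arm looks better with no true effect, and the final 15 versus 15 shows no trace of it.

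The rule also sits badly with the rest of the plan. It sets an arm-by-arm completer count that paired randomisation cannot aim at, and it makes the number randomised open-ended where other text fixes it at 30. In a trial meant to inform a larger one, the number lost from each arm is a main planning quantity, yet it is not among the listed measures.

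**Working it through.** **1. The plan's own figure.** Inputs from the Power calculation section: "Setting the power at 0.95 and the two-sided alpha at 0.05"; a two-sample t test; effect sizes 2.76 and 1.38. Power comes from the noncentral t distribution with 2n − 2 degrees of freedom and noncentrality d·√(n/2).

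| d | n per arm | Power |
|---|---|---|
| 1.38 | 15 | 0.954 |
| 1.38 | 14 | 0.940 |
| 2.76 | 5 | 0.967 |
| 2.76 | 4 | 0.899 |

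The stated 15 and 5 per group reproduce exactly. Fifteen is therefore the number needed with data and contains no allowance for loss. Replacement stands in for that allowance.

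**2. Can paired randomisation give 15 and 15?** Drop-out rates from here on are assumptions, because the article gives none.

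- With 15 randomised per arm and 20% drop-out in each, the chance of equal losses is the sum of squared Binomial(15, 0.2) probabilities, which is 0.18. In about 82% of trials the arms would need different numbers of replacements.
- Suppose blocks of two simply continue until both arms have at least 15 completers. The chance of ending at exactly 15 and 15 is about 26%, 20% and 17% at 10%, 20% and 30% drop-out. Otherwise one arm overshoots.
- At 20% drop-out, continuing in this way takes about 40 randomised on average. The simpler figure, 15/0.8 = 18.75, rounded up to 19 per arm and 38 in total, meets the target only in expectation.

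**3. Bias from conditioning on completion.** Simulation with no true effect and 15 completers per arm reached by replacement. A patient drops out when a latent variable, correlated with outcome, falls below the drop-out quantile. The two arms are compared by t test.

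| Drop-out, arm 1 vs arm 2 | Correlation with outcome | Mean difference (SD) | Type I error |
|---|---|---|---|
| 20% vs 20% | 0 to 0.8 | about 0 | about 0.05 |
| 30% vs 10% | 0 | about 0 | about 0.05 |
| 30% vs 10% | 0.5 | 0.15 | 0.07 |
| 30% vs 10% | 0.8 | 0.25 | 0.12 |
| 40% vs 10% | 0 | about 0 | about 0.05 |
| 40% vs 10% | 0.5 | 0.22 | 0.10 |
| 40% vs 10% | 0.8 | 0.36 | 0.20 |

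Extreme bound: exactly the worst fraction q leaves one arm and nobody leaves the other. The completer mean then shifts by φ(z_q)/(1 − q):

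- q = 0.1: 0.1755/0.9 = 0.195 SD
- q = 0.2: 0.2800/0.8 = 0.35 SD
- q = 0.3: 0.3477/0.7 = 0.50 SD

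Steps 2 and 3 answer different questions. The 82% assumes equal drop-out rates, at which the bias is about nil, so the two results must not be combined into one scenario.

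**4. Cost of not replacing.** At 20% loss, 15 × 0.8 = 12 per arm have data, and power at d = 1.38 is 0.898.

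**The case against.** The best defence is that the sentence sets an enrolment target inside a power calculation and does not define an analysis set. The Data analysis plan names none, and a separate analysis plan could keep everyone randomised. Replacement by itself does not prevent that. A reader might infer that the trial will analyse completers only. The article does not say so. What it does fix is a final sample defined by completion, and an analysis of all randomised patients would have to override that wording.

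A reader might also infer that replacements will be assigned without randomisation. This too is not stated. The same section calls 15 a minimum, and on that reading blocks of two can continue until both arms reach it. What stands is that exactly 15 and 15 generally needs directed replacement, and that the allocation of replacements is left open.

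The conflict with 30 randomised is mild. Elsewhere the article calls 30 a target, and the Power calculation section gives the 30 and the contingency together. Even so, the abstract's figure cannot survive a single replacement.

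It would be too strong to say that the rule masks attrition. Nothing forbids counting drop-outs, missing data are to be documented, and attendance would show part of the loss. Nor does the rule cause the gap in satisfaction ratings: these are taken at session 8, so early leavers are absent with or without replacement.

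Finally, bias requires drop-out that is both different between arms and related to outcome, and nothing in the article shows that this will occur.

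**Conclusion.** The point holds in a limited form. The replacement sentence defines the final sample by completion within each arm. That target does not fit 1:1 blocks of two, the allocation of replacements is unstated, and the 30 randomised cannot hold once a patient is replaced. Retention is not a listed feasibility measure.

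The size of the bias rests wholly on assumed drop-out. A moderate case is 0.15 to 0.25 SD with type I error of 0.07 to 0.12, at 30% versus 10% and a correlation of 0.5 to 0.8 with outcome. The 0.195 to 0.50 SD range is an extreme bound, and equal or non-informative drop-out gives about none. The simulation uses an unadjusted t test, so it indicates scale and does not predict the result of the planned ANCOVA.

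Because the analysis is primarily descriptive and the trial is an exploratory pilot, this is something that should be fixed; it does not invalidate the trial.

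**What to change.** Replace the drop-out sentence with three statements:

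1. All randomised patients are analysed in their assigned arm with all available data, including those who drop out.
2. Any patient added to offset losses enters only through the ordinary concealed randomisation sequence. Fifteen per arm with data is a target and not an exact completer count.
3. Drop-out and session attendance are reported by arm, over all randomised patients, as feasibility results.

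The abstract's 30 should then be worded to agree with whichever enrolment option is chosen. The planned ANCOVA need not be exchanged for another model to cure this point.

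The change is one of wording, and the Trial status section says that recruitment has not started. There is a price on one side or the other. If enrolment stays at 30, power at d = 1.38 is about 0.90 in place of 0.95 at an assumed 20% loss. If 15 completers in both arms are wanted through ordinary blocks, about 40 must be randomised at that same assumed loss.

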#### Ethics issues

No invasive procedure/test will be performed and no drug administrated. During the study (from the signature of informed consent to the study termination), any clinical event will be registered in a case report form. There are no documented side effects due to WBT [19–21] or the control condition.

## Discussion

The pharmacological treatment of chronic migraine has achieved remarkable progress in recent years [52, 53]. However, significant issues persist in patients who do not benefit from current drug treatments [54, 55] or for those with limited access to innovative approaches, such as anti-calcitonin gene-related peptide monoclonal antibodies, due to financial constraints. Current evidence on the efficacy of psychological interventions remains limited and unsatisfactory [8–18]. This study proposes a method aimed to empirically evaluate whether WBT provides a beneficial effect in chronic migraine patients. In particular, the present pilot study aims to test WBT versus a control condition as a psychological intervention for chronic migraine. The randomized trial represents a step towards the management of chronic migraine by means of psychological interventions.

We acknowledge some limitations of the study. Inclusion and exclusion criteria are proposed to maximize the safety of enrolled patients. However, such restrictions may reduce the possibility of generalization of results to the patient population with a more severe condition or those with high degrees of comorbidity. In addition, the sample size will not allow to test for potential differences in outcome between different durations of the chronic migraine or diverse levels of severity. Further, several key questions remain and could be the object for future studies, including whether, and at what size, differences in patient motivation or in the clinician–patient relationship may affect the outcomes. Should results of this pilot exploratory trial support our hypothesis, the next step will be a second trial enrolling a larger number of chronic migraine patients with a randomized and controlled multicentric design to investigate efficacy and potential mediators of treatment effects.

### Trial status

Participant recruitment has not started.

## Abbreviations

DSM: Diagnostic and Statistical Manual of mental disorders
IEs: independent evaluators
RAs: research assistants
WBT: well-being therapy
